## Abstract

(1) Background: Individuals with multiple sclerosis (MS) have to deal with numerous symptoms that adversely impact their quality of life. While pharmaceutical treatments offer some relief, they often fall short of addressing the full spectrum of MS symptoms. To bridge this gap, we introduce the Be Cool rehabilitation program, a comprehensive protocol designed to enhance the well-being and life quality of MS individuals. (2) Methods: The Be Cool program is a multifaceted approach that combines exercise training, nutritional guidance, psychological support, and cooling strategies. Adapted to meet the unique needs of MS individuals, this program aims to mitigate symptoms, promote physical and mental health, and improve overall quality of life. The integration of these strategies addresses the complex challenges faced by MS individuals, offering a holistic solution beyond conventional medication. (3) Conclusions: The Be Cool rehabilitation protocol is designed to offer individuals with MS a comprehensive approach to symptom management, fostering improvements in their quality of life. By addressing the multifaceted nature of MS through an integrated strategy, the program holds promise for more effective management of the condition.

## 1. Introduction

*“Our body has the ability to heal itself. Diet, exercise, environment, lifestyle and way of thinking are of utmost importance.”*
Hippocrates 460–377 BC

Multiple sclerosis (MS) is a chronic, debilitating disease of the central nervous system, predominantly affecting young adults [1]. This disease progressively impairs mobility and functionality, making everyday activities, community engagement, and personal care difficult for those diagnosed with MS. Although pharmaceutical treatments are essential for managing the condition, they may not address all symptoms, potentially affecting the individual’s quality of life [2]. People living with MS often deal with a spectrum of motor and psychological symptoms, which presents a complex challenge in terms of management [3]. While medications can mitigate some symptoms, they may worsen others, underscoring the necessity for a comprehensive and holistic treatment approach. To address this complexity, a comprehensive and multidisciplinary rehabilitation strategy is essential for enhancing the quality of life of individuals with MS.

Previous evidence has proved that regular physical activity is essential in managing MS [4,5]. Exercise not only helps maintain physical strength and endurance but also contributes to better balance and coordination, potentially reducing the risk of falls [6]. Moreover, it can have a positive impact on fatigue and fatigability, which are the most common and debilitating symptoms of MS [7]. Adapted exercise programs, considering individual capabilities and limitations, can significantly enhance the quality of life for MS individuals [8,9]. Even Uthoff’s syndrome, characterized by a temporary worsening of MS-related neurological symptoms due to increased core body temperature, may be managed effectively through exercise combined with cooling strategies [10,11]. These strategies, when applied before or during exercise, can prevent a rise in both core and skin temperatures, thereby enhancing the safety and effectiveness of exercise programs for individuals with MS. Research has demonstrated that such cooling strategies can significantly mitigate the risk of symptom exacerbation, enabling a more comfortable and beneficial physical activity experience for those affected by MS [12]. This form of therapy can be an essential component of symptom management, especially for those who experience a significant worsening of symptoms with heat.

Another critical component for overall health and well-being is balanced nutrition, particularly for individuals with MS. A strong nutritional foundation is essential in managing symptoms, mitigating inflammation, and supporting a robust immune system for those affected by MS. Individualized nutritional strategies that emphasize whole foods, anti-inflammatory components, and sufficient hydration are essential [13]. Malnutrition, often a concern among MS individuals, is closely associated with increased fatigue. Incorporating a diet rich in essential nutrients, such as vitamin D, biotin, and other vital vitamins and minerals, can significantly alleviate fatigue and aid in managing the challenging symptoms of MS [14]. However, there is a pressing need for educational initiatives to guide individuals with MS on the specific dietary choices that best support their unique health requirements, providing insight into beneficial ingredients and optimal nutritional practices.

Psychological support is essential for the mental health and well-being of individuals with MS, in addition to exercise, cooling strategy, and nutrition. Group counsellinginterventions provide a unique opportunity for people living with MS to receive emotional support and share everyday experiences and coping strategies [15,16]. This kind of psychological support can have profound effects on well-being, as it addresses both the psychological and emotional challenges that come with MS [17]. Psychological interventions, such as mindfulness, cognitive, behavioural therapy, and self-help groups, promote a range of positive psycho-social outcomes, such as reducing feelings of isolation, providing valuable information, and offering encouragement from those who truly understand the daily challenges faced by those living with MS [18,19]. A well-rounded rehabilitation protocol that integrates exercise, nutritional guidance, group psychological support, and a cooling strategy can offer a more effective way to manage the myriad symptoms associated with MS. This holistic approach acknowledges the diverse needs of individuals living with MS, aiming to provide relief not just from physical symptoms but also to support mental and emotional well-being. Such a protocol not only helps in symptom management but also contributes to overall life satisfaction, wellness, resilience, and quality of life for those battling this challenging condition.

In this light, we integrate these four components into a holistic combined rehabilitation protocol, which offers a comprehensive approach to managing MS symptoms. This holistic strategy addresses not only the physical aspects of the disease but also the emotional, psychological, and nutritional needs, thereby aiming to improve the overall quality of life for individuals with MS. The collaboration of healthcare professionals from various fields, including neurology, clinical exercise physiology, nutrition, and psychology, is vital in designing and implementing an effective rehabilitation plan. We hypothesize that compared to the control arm (usual care), Be Cool participants will show more significant improvements in the primary outcome of health-related quality of life (QoL) and in the secondary outcomes of functional ability, thermoregulation, nutritional status, mood, well-being, and psychological resilience.

## 2. Materials and Methods

The protocol received ethical approval from the ethics committee of the Greek Multiple Sclerosis Society (9 May 2023, internal ref: 396/23) and is registered at ClinicalTrials.gov: NCT06248281. The participants are being recruited from the Greek Multiple Sclerosis Society (https://gmss.gr/, accessed on 22 January 2024) (GMSS) via community outreach.

### 2.1. Eligibility Criteria

Prospective participants are eligible for the study if they meet the following criteria: they have a confirmed diagnosis of MS according to the McDonald criteria [20], exhibit the relapsing-remitting MS (RRMS) phenotype characterized by clearly defined attacks of new or increasing neurological symptoms, have experienced no relapses in the past six months, are between the ages of 20 and 60 years, have a confirmed diagnosis of MS for at least two years, and exhibit mild or moderate neurological disability, as defined by scoring between 0 to 5.5 on the Expanded Disability Status Scale (EDSS), indicating their ability to walk independently for at least 100 m without a cane [21].

The study will not include participants who have undergone psychotherapy in the past six months. Additionally, those with severe suicidality, including ideation, plan, and intent, or who have experienced one or more relapses in the previous month, have undergone corticosteroid treatment in the last month, have other severe medical conditions in addition to MS, or are currently pregnant, will not be able to participate in the study. After baseline testing, the principal investigator will perform randomization using sealed envelopes to allocate participants in a 1:1 ratio to either the BeCool or Control group.

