### 2.2. Recruitment and Trial Procedures

A promotional flyer, providing an overview of the program and contact information, was disseminated through social media channels such as Facebook, Instagram, and Twitter, as well as via email and to members of the Greek MS Society. Interested individuals were then contacted by either the Principal Investigator or representatives from the Greek MS Society’s center. Those meeting the study’s inclusion criteria were invited for a consultation, during which the study’s objectives and methodologies were explained, and a questionnaire was administered to confirm eligibility. Participants who consented to join the study attended a preliminary session for a comprehensive evaluation by a neurologist and to familiarize themselves with the experimental procedures. Subsequently, each participant was scheduled for an experimental session, which lasted for 120 min. To ensure a comprehensive evaluation of the intervention’s impact, a team of professionals from different disciplines, including clinical exercise physiology, nutrition, psychology, and environmental physiology, conduct the assessments. Enrolled participants are encouraged to continue with their usual care, which may vary based on factors such as disability status and disease severity. The usual care often includes services such as disease-modifying treatments, various aids, and physical or occupational therapy, all of which are essential for managing the condition and ensuring optimal support. However, to prevent potential confounding effects on the study outcomes, participants are advised to refrain from participating in structured exercise programs or psychological therapy during the intervention period. This ensures that any changes observed in the study are attributed specifically to the intervention being tested rather than to additional interventions that participants may undergo concurrently. Before, after three months, and after the six months of the Be Cool program, all the participants will attend an experimental session where they will undergo the following assessments.

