### 2.10. Blinding

Randomization will be blinded to outcome assessors and the statistician. A blinded interpretation of the study results will also be conducted [29].

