## 3. Data Analysis

### 3.1. Sample Size Calculation

Our study evaluates the effects of a holistic rehabilitation program on individuals with MS, utilizing key metrics to determine improvements in functional ability, nutritional status, and psychological well-being. Determining the minimum required sample size for our protocol was guided by preliminary data on quality of life [30]. Sample size calculations were performed using G*Power 3.0 [31], employing the “ANOVA: Repeated measures, within-between interaction” approach. This method facilitated estimating the study’s power to detect between-group differences and within-subject changes over time, considering three measurement points (baseline, mid-intervention, and post-intervention) for our MS participants. We set the statistical power and α error probability at 0.90 and 0.05, respectively, aligning with rigorous research standards to ensure sufficient sensitivity in detecting meaningful effects. Our calculations indicate that each group requires 15 individuals to power the study sufficiently. Analyses will adhere to the intention-to-treat principle, with multiple imputations used to handle missing data. A per-protocol and sensitivity analysis will also be conducted, excluding participants with significant non-compliance.

Detailed documentation and analysis of baseline demographics, including age, gender, disease duration, and relevant medical history, will provide valuable insights into the characteristics of our study population and allow us to control for potential confounding variables in our analyses. Additionally, thorough documentation of participants’ current disease-modifying therapy (DMT) regimens, including the type of medication, dosage, and duration of treatment, will enable us to assess the impact of DMT use on intervention outcomes and explore potential interactions with our intervention. We aim to conduct subgroup analyses to investigate differences in treatment effects based on baseline demographics and DMT use, with the goal of informing personalized approaches to MS management. By implementing these strategies, we aim to enhance the validity and generalizability of our findings and ultimately improve the care and outcomes of individuals living with MS.

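### The principal investigator may contact candidates and also performs the sealed-envelope randomisation, so allocation is not separated from recruitment

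*Protocol article*

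**What the plan says.** Four places in the protocol article bear on this point.

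- **Allocation (Section 2.1).** The text names both the person and the mechanism: "the principal investigator will perform randomization using sealed envelopes to allocate participants in a 1:1 ratio". The step follows baseline testing.
- **Recruitment (Section 2.2).** "Interested individuals were then contacted by either the Principal Investigator or representatives from the Greek MS Society’s center". At a later consultation "a questionnaire was administered to confirm eligibility", by someone not named. A neurologist evaluates those who consent, and a multidisciplinary team carries out the assessments.
- **Blinding (Section 2.10).** "Randomization will be blinded to outcome assessors and the statistician". The principal investigator is not mentioned, and neither are participants.
- **Size (Section 3.1).** "Our calculations indicate that each group requires 15 individuals to power the study sufficiently".

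The Introduction (Section 1) names health-related quality of life as the primary outcome. Section 2.6 lists the MSQOL-54, a questionnaire, as the quality-of-life instrument.

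**The concern.** Allocation concealment works when whoever deals with candidates can neither know nor influence the next assignment. The plan gives the allocation step to a role that may also be in contact with candidates, so the usual separation is missing by design.

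Two features of this trial make that separation more valuable than usual. First, one arm follows a six-month programme of exercise, nutrition, group psychology and cooling while the other follows usual care, so participants know their arm. They also report the primary outcome themselves, so blinded assessors protect it very little and sound allocation becomes the main safeguard against bias. Second, the arms are small, so each participant carries much weight in an arm mean. If a few more motivated people were steered towards Be Cool, the resulting difference could be mistaken for a treatment effect.

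**Working it through.** **Step 1. Set the roles side by side.**

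| Task | Who, according to the article | Section |
|---|---|---|
| Contact with interested people | Principal investigator or Society representatives | 2.2 |
| Eligibility questionnaire | Not named | 2.2 |
| Assessments | Multidisciplinary team | 2.2 |
| Randomisation by sealed envelope | Principal investigator | 2.1 |
| Blinded to allocation | Outcome assessors, statistician | 2.10 |

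The principal investigator appears in the contact row and the randomisation row, and is absent from the blinding row. This overlap is the finding, and it rests on stated text alone.

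**Step 2. Illustrate what one influenced allocation could do.** The plan has no figure of its own to reproduce here. The 15 per group is taken as given, and the point does not depend on how it was calculated. Inputs:

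- n = 15 per arm (Section 3.1; a calculated requirement, not a stated enrolment total).
- Assumption: one pair is exchanged between arms, and the two people differ by 1 SD in expected outcome for reasons the measured baseline does not capture.

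The Be Cool mean rises by 1/15 SD and the control mean falls by 1/15 SD, so the shift in the difference is 1/15 + 1/15 = 2/15 = 0.13 SD. Two such pairs give 4/15 = 0.27 SD.

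**Step 3. Put that on the scale of the trial's precision.** Assume an analysis of covariance on baseline with a baseline-to-outcome correlation of 0.5. Neither is stated in the article. Then

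SE = sqrt(2 × (1 − 0.5²) / 15) = sqrt(2 × 0.75 / 15) = 0.32 SD.

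One exchanged pair is 0.133 / 0.316 = 0.42 of a standard error. Two pairs are 0.267 / 0.316 = 0.84 of a standard error.

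**Step 4. Check what adjustment can repair.** Suppose instead that the pair differs by 1 SD in the measured baseline score. With the same correlation of 0.5, the expected outcome gap is 0.5 SD and the unadjusted shift is 0.5 × 2/15 = 0.067 SD. Adjustment for baseline brings this to about zero. The shift in Step 2 remains, because by assumption the trait behind it, such as motivation, is not in the model.

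**The case against.** The strongest reply is that the article says less than a suspicious reader might infer.

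- **Recruitment is shared.** Contact is by the principal investigator or by Society representatives, and nobody is named for the consultation or the eligibility decision. This stands. The text supports only that the principal investigator may contact candidates, not that this role decides who enters.
- **Knowledge of baseline results.** A reader might take "After baseline testing, the principal investigator will perform randomization" to mean that the results are seen before allocation. The article does not say so; Section 2.2 has "a team of professionals from different disciplines, including clinical exercise physiology, nutrition, psychology, and environmental physiology, conduct the assessments". Randomising after baseline is also the correct order, because it keeps the baseline measurements free of knowledge of the arm. This stands in full.
- **Custody of the envelopes.** A reader might infer that the principal investigator prepares and keeps them. The article does not say who generates the sequence or holds the envelopes. Those details, with opacity and numbering, may properly be left to the full protocol, so their absence is no finding.
- **Blinding is a different matter from concealment.** This is true, and Section 2.10 contains no error. It is relevant only because it does not offset the overlap of roles.
- **The numbers are invented.** The number of exchanges and the 1 SD gap are indeed assumptions, and Section 3.1 intends to control for potential confounders. That control helps for measured traits but not for unmeasured ones.

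One thing survives all of this. The full protocol could add safeguards around the envelopes, but it could not hand the randomisation to someone else without contradicting Section 2.1.

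**Conclusion.** The point holds as a cheap and worthwhile improvement. By the article's own account, a role that may contact candidates and is not listed as blinded also performs the randomisation.

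The size is illustrative only: 0.13 SD for each exchanged pair that differs by 1 SD in unmeasured prognosis, with 15 per arm. On the assumed correlation of 0.5, that is about two fifths of a standard error. The article gives no basis for estimating how many allocations, if any, would be affected.

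Stronger conclusions are not supported. The text does not show that the investigator selects on baseline results or controls the envelopes. It would also be wrong to say that analysis could repair nothing, since selection acting through the measured baseline would largely be removed by adjustment. The finding concerns a vulnerability and does not allege misconduct.

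**What to change.** Keep randomisation after baseline testing. Replace allocation by the principal investigator with one of the following:

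1. A web-based tool that releases the arm only after the participant's ID and completed baseline have been entered, working from a computer-generated list unknown to the principal investigator.
2. If envelopes are to stay, allocation by an existing staff member outside recruitment, delivery and assessment, from sequentially numbered opaque envelopes, with the participant's ID written on each before it is opened.

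Amend Section 2.1 to name who allocates. Section 2 describes recruitment as under way, so for any participants already allocated, report the method actually used.

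The cost is a small set-up effort. No extra visits or staff are needed, and no sample-size figure changes.

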### 2.2. Recruitment and Trial Procedures

A promotional flyer, providing an overview of the program and contact information, was disseminated through social media channels such as Facebook, Instagram, and Twitter, as well as via email and to members of the Greek MS Society. Interested individuals were then contacted by either the Principal Investigator or representatives from the Greek MS Society’s center. Those meeting the study’s inclusion criteria were invited for a consultation, during which the study’s objectives and methodologies were explained, and a questionnaire was administered to confirm eligibility. Participants who consented to join the study attended a preliminary session for a comprehensive evaluation by a neurologist and to familiarize themselves with the experimental procedures. Subsequently, each participant was scheduled for an experimental session, which lasted for 120 min. To ensure a comprehensive evaluation of the intervention’s impact, a team of professionals from different disciplines, including clinical exercise physiology, nutrition, psychology, and environmental physiology, conduct the assessments. Enrolled participants are encouraged to continue with their usual care, which may vary based on factors such as disability status and disease severity. The usual care often includes services such as disease-modifying treatments, various aids, and physical or occupational therapy, all of which are essential for managing the condition and ensuring optimal support. However, to prevent potential confounding effects on the study outcomes, participants are advised to refrain from participating in structured exercise programs or psychological therapy during the intervention period. This ensures that any changes observed in the study are attributed specifically to the intervention being tested rather than to additional interventions that participants may undergo concurrently. Before, after three months, and after the six months of the Be Cool program, all the participants will attend an experimental session where they will undergo the following assessments.

### 2.3. Physiological Measurements

Core temperature (index by visceral temperature) will be recorded continuously using a non-harmful telemetric capsule (e-Celsius Performance, BodyCap, Caen, France). Skin temperatures will be continuously recorded at four sites using iButton temperature sensors (DS1921 H, Maxim/Dallas Semiconductor Corp., Dallas, TX, USA). Specifically, skin temperature will be measured at the upper arm, chest, thigh, and calf, which will be used to estimate mean skin temperature (upper arm: 30%, chest: 30%, thigh: 20%, and calf: 20%). Finally, heart rate will continuously be recorded via a Polar S810 (Kempele, Finland).

